### Dropout criteria

3.3

Participants may withdraw from the study at any time for any of the following reasons: (i) desire to leave the study (ii) non-compliance or refusal to cooperate with study procedures or investigators (iii) a medical condition that, in the investigator’s judgment, contraindicates further participation. In each case, the reason for withdrawal will be documented in the study records.

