According to the World Health Organization [WHO] (2020) guidelines, there is a dose–response relationship between physical activity and health outcomes, with greater health benefits achieved with increasing amounts of physical activity, and the largest relative gains observed when moving from inactivity to moderate activity levels. Consistently, our ongoing study (Rotondo et al., 2024) suggests a similar dose–response effect in individuals with PD, where higher volumes of structured exercise (expressed in MET-minutes per week) are associated with improvements in both functional outcomes and peripheral biomarkers. In this regards, participants to PRIME study will follow World Health Organization [WHO] (2020) recommendations for adults, including those aged ≥ 64 years: 150–300 min/week of moderate-intensity aerobic physical activity; or 75–150 min/week of vigorous-intensity aerobic physical activity, corresponding to approximately 500–1,000 MET-min per week (moderate intensity: 3.0–5.9 METs; vigorous intensity: ≥6.0 METs); or an equivalent combination; plus muscle-strengthening exercises of moderate or higher intensity for all major muscle groups on ≥2 days/week. The daily intensity and weekly volume of physical exercise will be supervised by Adapted Physical Activity Specialists and health professionals, and monitored via smartwatch.

Group C (A + B): Mediterranean diet + intensive physical activity combined intervention

Participants will concurrently adhere to the dietary and physical-activity protocols described above.

Group D: controls

Participants will continue usual PD management according to clinical guidelines, without any additional specific dietary or exercise interventions provided from the study. To quantify potential contamination, diet adherence and physical activity levels will also be monitored in the control arm using the same dietary adherence tools (MediLITE and structured dietary records) and standardized physical-activity questionnaires/brief activity logs.

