## Statistical analysis

4

Statistical analyses will be conducted using IBM Statistical Packages for Social Science Software (SPSS) version 23 (IBM Corp., Armonk, NY, United States) and R (R Foundation for Statistical Computing, Vienna, Austria) for microbiome-specific analyses. A *p*-value < 0.05 will be considered statistically significant for the prespecified primary analysis; multiplicity control will be applied where appropriate for exploratory high-dimensional microbiome analyses using false discovery rate procedures (e.g., Benjamini–Hochberg). Baseline characteristics will be summarized using descriptive statistics [mean ± standard deviation (SD) for normally distributed data, or as median with interquartile ranges (IQR) in case of asymmetric distributions]. Categorical variables will be expressed in terms of absolute frequencies and percentages. Comparisons across the four study groups will be conducted using statistical tests appropriate to the data type and distribution for outcomes assesses at a single time point (ANOVA or Kruskal-Wallis for continuous variables; Chi-square/Fisher’s for categorical variables). Given the longitudinal design (T0, T1, FU1, FU2), outcomes measured repeatedly over time will be analyzed using mixed-effects models to account for within-participant correlation. Analyses will be conducted primarily under an intention-to-treat principle; sensitivity analyses will assess the impact of missing data where relevant. For continuous outcomes, linear mixed-effects models will include fixed effects for time, diet, exercise, and their interactions (time × diet × exercise) (or time × trial arm), and a random intercept for participant. For non-normally distributed outcomes, appropriate transformations or generalized mixed models will be considered. The prespecified primary contrast will focus on the change from T0 to T1 in the combined intervention versus standard care (control); analyses including FU1 and FU2 will be considered secondary/exploratory and reported as durability/maintenance assessments. In addition, subgroup analyses will be conducted to explore potential heterogeneity of intervention effects by disease stage (I/II/III of H&Y), age group, and gender, where sample size permits, with results interpreted as exploratory. Sensitivity analyses will be conducted to assess the robustness of findings, including adjustment for prespecified covariates and assessment of protocol adherence where relevant.

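### Section 3.3 lets non-compliance end study participation, which is in tension with the intention-to-treat principle because loss of T1 samples can then depend on adherence

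*Protocol article*

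**What the plan says.** Section 3.3 (Dropout criteria) opens with "Participants may withdraw from the study at any time for any of the following reasons" and gives three grounds: a wish to leave, "ii) non-compliance or refusal to cooperate with study procedures or investigators", and a medical condition that in the investigator's judgment rules out continuing. The action it attaches is "In each case, the reason for withdrawal will be documented in the study records". Nothing is said there about further visits or samples.

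Section 4 (Statistical analysis) states: "Analyses will be conducted primarily under an intention-to-treat principle; sensitivity analyses will assess the impact of missing data where relevant". Its later list of sensitivity analyses ends with "including adjustment for prespecified covariates and assessment of protocol adherence where relevant". On the main comparison it says "The prespecified primary contrast will focus on the change from T0 to T1 in the combined intervention versus standard care (control"). Sections 3.5.1 and 4.1 define the primary endpoint as the T0–T1 change in Bray–Curtis dissimilarity, tested by PERMANOVA with permutations restricted within participants.

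Section 3.4.5 describes Group D as continuing usual management "without any additional specific dietary or exercise interventions provided from the study", while Group C follows both programmes.

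**The concern.** An intention-to-treat comparison needs outcomes from people who did not follow their assigned programme as well as from those who did. Section 3.3 offers a way out of the study, not merely out of the programme, for people who have neither asked to leave nor have a medical reason. If it is used for poor adherence, T1 data go missing because of adherence.

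The primary contrast sets the arm with two programmes to follow against the arm with none, so such losses need not balance. The trial is also open-label (section 3.4.1), and no threshold for non-compliance is given, so applying the ground is a matter of judgment by staff who may know the allocation. Section 3.2 says the pilot is meant to supply effect-size estimates for a definitive trial, so a bias here would carry into that trial's planning.

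**Working it through.** The plan gives no figure on this point to reproduce. The check is mainly a reading of sections against each other, followed by one illustration.

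**1. Is the second ground distinct?** Yes. It stands beside a wish to leave and a medical condition, so it covers participants to whom neither of those applies.

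**2. What does it end?** Participation in the study. Section 3.3 requires only that the reason be recorded.

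**3. What does the primary analysis need?** Stool at both T0 and T1. Someone with T0 only has no T0–T1 change and nothing to permute within participant, whatever arm they are counted in.

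**4. Who is exposed?** A, B and C have a diet or exercise programme to fail, and C has both. D has neither. D does have study procedures: stool, blood, saliva and urine at each visit (section 3.4.4), plus MediLITE, dietary records and activity questionnaires or logs (section 3.4.5). The ground can therefore apply in all four arms. An imbalance is plausible but is not written into the rule.

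**5. Illustration for a mean difference.** These assumptions are not in the documents: adherers in C gain an effect of 1 relative to D; a share q of C gains 0; all of that share are withdrawn without T1 data; D loses nobody.

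- All randomised: (1 − q) × 1 + q × 0 = 1 − q
- Only those remaining: 1
- Ratio: 1/(1 − q)

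| Assumed q | All randomised | Remaining | Overstatement |
|---|---|---|---|
| 0.1 | 0.9 | 1.0 | 1/0.9 = 1.11 (11%) |
| 0.2 | 0.8 | 1.0 | 1/0.8 = 1.25 (25%) |
| 0.3 | 0.7 | 1.0 | 1/0.7 = 1.43 (43%) |

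This is a worst case for a difference in means. The PERMANOVA pseudo-F and R² do not scale by this factor, so the percentages are not the bias of the planned primary test.

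**6. Attrition.** Section 3.2 allows about 10% and applies it to the total: 0.10 × 80 = 8 participants. At q = 0.2, C loses 0.2 × 20 = 4, which is 4/80 = 5% of the total. That exceeds the allowance only if it is read per arm (0.10 × 20 = 2), and the article does not apply it that way.

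**The case against.** A reader might infer three stronger things, and the article supports none of them.

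- *Section 3.3 contradicts intention-to-treat.* Intention-to-treat governs who is analysed and in which arm. No section removes withdrawn or non-compliant participants from the analysis, and sensitivity analyses for missing data are planned. The planned assessment of adherence also presupposes that some non-adherers have data. Tension is the accurate word.
- *The rule selectively removes non-adherers from the intervention arms.* The wording is permissive, covers every arm and refers to study procedures and investigators, not to the programmes by name. The response to poor adherence that section 3.4.5 describes is support through reminders, calls and visits.
- *The primary analysis becomes an analysis of compliers.* That would follow only if non-adherers were in fact withdrawn and their T1 samples not obtained.

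It can also be said that handling of data after withdrawal belongs in the full protocol or the analysis plan, neither of which is shown. That would answer a complaint about a missing detail. Here the article states a rule under which non-compliance is a reason to leave the study, and that statement needs to agree with section 4. The planned sensitivity analyses can probe the effect of lost T1 samples but cannot replace samples never collected, and the adherence analysis would lack the participants it most needs.

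Finally, removing the whole second ground would go too far: someone who refuses stool collection cannot supply a T1 sample under any wording.

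**Conclusion.** The point holds as a tension to be reconciled, and it should be resolved before T1 collection because lost samples cannot be recovered later. As worded, section 3.3 permits adherence-related loss of T1 data, plausibly greater in A–C than in D and greatest in C. If non-adherers would have shown less change than adherers, the likely direction is overstatement of the C versus D effect. The size cannot be derived from the documents: no non-compliance rate is given, and the illustrative factor 1/(1 − q) rests on an assumed q, total loss of T1 data in that share, no effect in that share, no loss in D, and a mean-difference scale. If no participant is withdrawn for non-adherence, or if T1 samples are obtained regardless, this bias does not arise.

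**What to change.** Reconcile section 3.3 with section 4:

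- State that non-adherence to the diet or exercise programme does not by itself end study participation.
- State that such participants, if they still consent, are invited to give the T1, FU1 and FU2 samples and assessments, and are analysed in their randomised arm.
- Describe adherence from MediLITE, the dietary records and the smartwatch data, and use it in the sensitivity analysis already planned.
- Leave withdrawal of consent, refusal of the assessments themselves and the medical ground as written.

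The cost is a few sentences of wording and some extra attempts to bring non-adherent participants to visits already scheduled. The effect estimate may come out smaller, but it would better reflect everyone randomised.

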### Procedures

3.4

At screening visit, demographic data, disease duration and detailed medical history including medications will be collected. Then, all participants will undergo comprehensive neurological and neuropsychological evaluations, including the administration of standardized neuropsychological tests and scales, such as MoCA, MMSE, and BDI-II. The disease stage will be assessed using modified H&Y scale, while participants will also complete a detailed 3-days dietary record for nutritional assessment (see Supplementary Table 1).

#### Randomization, timeline and masking

3.4.1

Enrolled participants will be sequentially randomized upon receipt of informed consent and availability of medical records, using a computer-generated, permuted-block scheme (1:1:1:1) prepared in advance by an independent statistician. Allocation will be stratified by disease stage and age group to ensure balance across arms. Each participant will be informed of their assignment at the baseline visit (T0). Moreover, given the nature of the dietary and physical-activity interventions, this is an open-label trial and participants and intervention providers cannot be blinded. To mitigate performance and assessment bias, all clinical assessments will be performed according to standardized operating procedures and by trained assessors, following a prespecified assessment order. Motor assessments will be performed in the ON state and scheduled at a consistent time relative to the participant’s usual dopaminergic medication intake across visits. Patient-reported questionnaires will be administered using standardized instructions and the same mode of administration across visits. Laboratory and bioinformatics analyses will be performed on coded samples, with analysts blinded to group allocation and timepoint. To ensure data integrity, a researcher non-involved in clinical evaluation or in the collection and management of biological samples, will enter the information into the database.

The study timeline (Figure 2) comprises four clinical assessments and concomitant biological sample collections:

**FIGURE 2 F2:**
[figure not shown]
Organization of the intervention study. T0, baseline (week 0); T1, end of intervention (week 24); FU1, first follow-up (week 36); FU2, second follow-up (week 48).

T0 (baseline): pre-intervention assessment (Week 0)T1 (end of intervention): 6 months after the start of the intervention (Week 24)FU1 (first follow-up): 3 months post-intervention (Week 36)FU2 (second follow-up): 6 months post-intervention (Week 48).

This longitudinal design allows sufficient time to characterize temporal changes in GM composition and diversity (Clauss et al., 2021; Pagliai et al., 2020).

#### Anthropometric and body composition

3.4.2

A registered nutritionist will measure each participant’s height and weight to calculate BMI, and will assess body composition using a Bioelectrical Impedance Analyzer device (TANITA).

#### Physical exercise supervision

3.4.3

Physical exercise sessions will be supervised by health professionals and Adapted Physical Activity Specialists to ensure safety, proper technique, and adherence to the training protocol, as well as to guarantee accurate quantification of daily exercise intensity and weekly exercise volume. Physical activity will also be monitored using a smartwatch to record and quantify individual exercise parameters. To further ensure participant safety, falls will be prospectively recorded at each visit and through falls diary completed by participant, and musculoskeletal adverse events (e.g., muscle strain, joint pain, or injury) will be systematically assessed.

#### Collection and storage of biological samples

3.4.4

Biological samples will be collected at each outpatient visit and all samples will be processed according to standard operating procedures and stored under optimal conditions. Specifically, 10 mL of blood will be collected in ethylenediaminetetraacetic acid (EDTA) tubes for Ficoll-Paque density gradient plasma separation and peripheral blood mononuclear cells (PBMCs) isolation; an additional 6 mL in EDTA tubes for plasma multiplex immunoassay (Luminex) and 5 mL in serum-separator tubes for future research analysis will be collected (Becton-Dickinson).

For the fecal samples, participants will be instructed to collect approximately 10 g of feces into two pre-labeled tubes, one of which contains an appropriate preservative solution. One tubes will be used for microbiome analysis, the other for further research about SCFA analysis. During each visit, a total of 4 ml of saliva will be collected in two cryovials for Extracellular Vesicles (EVs) and oral microbiota analysis. In addition, a urine sample will be collected for further biochemical and microbiological assays. Each specimen will be labeled with a unique participant code, recorded in a secure biorepository database, and stored in accordance with best clinical practices. The samples will be kept for the duration of the project, exclusively for research purposes; any use or disposal will be properly documented.

#### Intervention groups

3.4.5

Eligible participants will be randomized to one of four six-month arms (Figure 2):

Group A: Mediterranean diet

Participants will receive a detailed and personalized 7-days menu (specifying food ingredients by weight and/or volume), developed by a nutritionist considering: (1) PD pharmacological treatment timing and absorption interaction, (2) core Mediterranean diet principles and (3) typical Italian meal patterns (e.g., five daily eating occasion). No food category will be excluded *a priori*; however, red and processed meats will be limited to once per week, poultry to ≤3 servings/week and fish to 2/3 servings/week. Substitutions will be provided. Macronutrient targets are approximately 25%–30% of energy from fats, 15%–20% from proteins and 55%–60% from carbohydrate (primarily complex). In particular, extra-virgin olive oil will be recommended as the main added fat; daily intake of plant foods (fruit/vegetables and legumes) and preference for whole-grain products will be emphasized; and added sugars and ultra-processed foods will be discouraged. No meals or supplements will be provided. Participants will prepare their own meals or eat at a restaurant. Dietary adherence will be assessed using a validated Mediterranean diet adherence questionnaire (the MediLITE) (Sofi et al., 2017), administered at each timepoint. This will be complemented by structured dietary records (e.g., 3-day food diaries - including one weekend day) collected periodically to quantify key components; participants will receive prior standardized training to ensure accurate and consistent completion of the records.

Group B: intensive physical activity

According to the World Health Organization [WHO] (2020) guidelines, there is a dose–response relationship between physical activity and health outcomes, with greater health benefits achieved with increasing amounts of physical activity, and the largest relative gains observed when moving from inactivity to moderate activity levels. Consistently, our ongoing study (Rotondo et al., 2024) suggests a similar dose–response effect in individuals with PD, where higher volumes of structured exercise (expressed in MET-minutes per week) are associated with improvements in both functional outcomes and peripheral biomarkers. In this regards, participants to PRIME study will follow World Health Organization [WHO] (2020) recommendations for adults, including those aged ≥ 64 years: 150–300 min/week of moderate-intensity aerobic physical activity; or 75–150 min/week of vigorous-intensity aerobic physical activity, corresponding to approximately 500–1,000 MET-min per week (moderate intensity: 3.0–5.9 METs; vigorous intensity: ≥6.0 METs); or an equivalent combination; plus muscle-strengthening exercises of moderate or higher intensity for all major muscle groups on ≥2 days/week. The daily intensity and weekly volume of physical exercise will be supervised by Adapted Physical Activity Specialists and health professionals, and monitored via smartwatch.

Group C (A + B): Mediterranean diet + intensive physical activity combined intervention

Participants will concurrently adhere to the dietary and physical-activity protocols described above.

Group D: controls

Participants will continue usual PD management according to clinical guidelines, without any additional specific dietary or exercise interventions provided from the study. To quantify potential contamination, diet adherence and physical activity levels will also be monitored in the control arm using the same dietary adherence tools (MediLITE and structured dietary records) and standardized physical-activity questionnaires/brief activity logs.

To optimize adherence to the program, reminders will be sent via phone calls, email or text message before each study visit. All participants will be followed up by physicians and nutritionists with weekly or monthly phone or videocalls or outpatient periodically visits to reinforce compliance, improve adherence to diet and/or physical activity, and monitor for adverse events. Physical exercise will be supervised and monitored by Adapted Physical Activity Specialists and health professionals to ensure safety, correct execution, and appropriate training progression.

### Study outcomes

3.5

#### Primary outcome

3.5.1

The primary endpoint of the PRIME study is to evaluate the effect of the interventions on GM β-diversity in PD patients, defined as the change in Bray-Curtis dissimilarity from T0 (baseline) to T1 (end of intervention). The prespecified primary contrast will be the between-group difference in the T0-T1 change in β-diversity for the combined intervention (Group C) versus standard care (Group D). As supportive primary microbiome descriptors, we will also quantify α-diversity and taxonomic composition/relative abundance, with analyses primarily intended to describe community structure and to support interpretation of β-diversity findings. Microbiome profiling will be performed using third-generation, high-resolution long-read sequencing technology, the Pacific Biosciences (PacBio) system, capable of sequencing amplicons up to ∼20,000 base pairs (bp) (Biada et al., 2025; Buetas et al., 2024). Exploratory microbiome aims will include (i) identification of stage-associated microbial patterns and candidate non-invasive microbiome biomarkers, treated as hypothesis-generating, and (ii) a methodological comparison between PacBio long-read sequencing and Illumina MiSeq short-read 16S rRNA amplicon sequencing. The comparison will evaluate relative performance in terms of taxonomic resolution and community profiling, with particular attention to the ability of PacBio to achieve higher resolution at the species level. We will also assess the degree of compositional similarity between microbial communities characterized by the two platforms, thereby determining the feasibility and potential benefits of integrating sequences from different technologies in microbiome research. FU1 and FU2 assessments will be used for exploratory analyses of the durability/maintenance of microbiome changes beyond the end of the intervention. Results from these exploratory analyses will be interpreted in the context of the pilot design.

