### Participants and eligibility criteria

3.2

The calculation of the sample size was not strictly required given the pilot nature of this study. Accordingly, the target sample size was primarily driven by feasibility considerations and the need to obtain precise effect-size estimates to inform a definitive RCT. However, to support the microbiome endpoint, we performed an *a priori* power assessment. Following the recommendations of Ferdous et al. (2022), we selected β-diversity as the primary endpoint to detect differences between groups in the composition of intestinal microbial species. Using G*Power version 3.1.9.7, assuming an effect size of (Cohen’s f) 0.25, a statistical power of 0.95 (1−β) and setting α to 0.05, we estimated the minimum required sample size. To account for expected attrition during the intervention and follow-up period (approximately 10%), the total sample size was increased to 80 participants (20 per arms). Participants will be recruited from Clinical Trial Centers for Parkinson’s Disease (RU1 - RU2) during routine clinical visits. A total of eighty (*n* = 80) participants meeting the following eligible criteria will be enrolled and randomly assigned to an intervention or to the control group:

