### Fecal microbiome processing, sequencing, bioinformatics, and statistical analysis

4.1

Fecal collection kits and detailed instructions will be provided to participants. Samples will be stored at −80 °C until processing. DNA will be extracted using the PowerSoil Pro DNA kit (Qiagen). For short-read profiling, the V4–V5 region of the 16S rRNA gene will be amplified using primers 515F and 926R with Illumina barcodes. For long-read profiling, the 16S-ITS-23S operon will be amplified with primers A515F and U2428R and PacBio barcodes to obtain amplicons > 3,500 bp. Sequencing of both short- and long-read libraries will be performed by the Sequencing Core at the University of Illinois at Urbana-Champaign (UIUC). Raw sequence data will be processed in the R statistical environment; DADA2, a bioinformatics pipeline, specifically developed for modeling and correcting amplicon sequencing errors (Callahan et al., 2016), will be used for quality assessment, length filtering, denoising high-quality reads into Amplicon Sequence Variants (ASVs) and chimera removal.

Given the complexity of the dataset, microbiome statistical analysis will be conducted using standardized and reproducible methodologies. α- and β-diversity analyses will be assessed at appropriate taxonomic levels, from phylum to genus, using the phyloseq package in R (McMurdie and Holmes, 2013). α-diversity will be estimated using indices such as Shannon, Simpson, and Faith’s phylogenetic diversity and between-group differences will be tested using appropriate non-parametric test (e.g., Kruskal-Wallis) for cross-sectional comparisons or generalized linear models adjusted for covariates. For longitudinal analyses across T0, T1, FU1, and FU2, mixed-effects models will be used where appropriate to account for repeated measures within participants. β-diversity will be quantified using distance metrics including Bray-Curtis, Jaccard, and weighted/unweighted Unifrac. The prespecified primary microbiome analysis will focus on Bray–Curtis β-diversity and will evaluate whether the change from T0 to T1 differs between the combined intervention (Group C) and standard care (Group D) using Permutational Multivariate Analysis of Variance (PERMANOVA). To account for the repeated-measures structure, permutation testing will be restricted within participants. FU1 and FU2 will be included in secondary/exploratory analyses of durability/maintenance.

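### The primary endpoint does not say which samples its Bray-Curtis dissimilarity compares, and two of its three readings are not what the named PERMANOVA tests

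*Protocol article*

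**What the plan says.** Section 3.5.1 of the protocol article describes the primary endpoint as "defined as the change in Bray-Curtis dissimilarity from T0 (baseline) to T1 (end of intervention". It adds: "The prespecified primary contrast will be the between-group difference in the T0-T1 change in β-diversity for the combined intervention (Group C", with Group D (standard care) as comparator.

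Section 4.1 assigns the test. It is to "evaluate whether the change from T0 to T1 differs between the combined intervention (Group C) and standard care (Group D", by PERMANOVA on Bray-Curtis distances. On the permutations it states: "To account for the repeated-measures structure, permutation testing will be restricted within participants". It does not name the model term (arm, time or arm by time) that carries the primary p-value.

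Section 4 applies a 0.05 threshold to the primary analysis and repeats the contrast: "The prespecified primary contrast will focus on the change from T0 to T1 in the combined intervention versus standard care (control". Section 3.2 supports the microbiome endpoint with a G*Power calculation "assuming an effect size of (Cohen’s f) 0.25", power 0.95 and α 0.05. With about 10% attrition this leads to 80 participants, 20 per arm. The G*Power test family and the number before attrition are not given.

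**The concern.** Bray-Curtis is a distance between two samples, so an endpoint built on it must say which two. Section 3.5.1 does not. The wording allows three quantities:

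1. **Within-participant distance**, BC(T0, T1): how far each person's community moved, without direction.
2. **Spread among participants** at each visit, and how that spread changes: dispersion.
3. **Arm-by-time shift**: whether community composition moved from T0 to T1 differently in C and in D, a question of location.

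PERMANOVA on the distance matrix addresses the third. The endpoint wording reads at least as naturally as the first or second. At stake is what a significant or null primary result would mean, and which effect size this pilot passes on to the definitive trial it is meant to inform.

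**Working it through.** **Step 1. The plan's sample size.** Inputs from 3.2: f = 0.25, power 0.95, α = 0.05, about 10% loss, total 80. I used noncentral-F power. A correlation of 0.5 between visits and sphericity are my assumptions.

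- One-way, 4 groups: 280 needed, 312 after loss. This does not give 80.
- Within-between interaction, 4 groups × 2 visits: λ = f²·N·m/(1−ρ). At N = 72, λ = 0.0625 × 72 × 2 / 0.5 = 18 on 3 and 68 df, power 0.948, and 72/0.9 = 80. Reaching 0.95 with equal arms needs 76, and 76/0.9 rounds up to 85.

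So 80 is nearly reproduced by one unstated design and is neither confirmed nor refuted. That design is an omnibus test over four arms, not C versus D.

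**Step 2. What f = 0.25 gives for C versus D.** After 10% loss, 20 × 0.9 = 18 per arm.

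| Quantity to which f is attached | λ at N = 36 | Power, 18 per arm | Power, 20 per arm |
|---|---|---|---|
| One number per participant, λ = f²N | 0.0625 × 36 = 2.25 | 0.31 | 0.34 |
| 2 arms × 2 visits interaction, ρ = 0.5 | 0.0625 × 36 × 2 / 0.5 = 9 | 0.83 | 0.87 |

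Neither reaches 0.95, and neither is the power of a PERMANOVA. The 0.95 has no defined link to the primary contrast.

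**Step 3. Can the stated test address reading 1?** BC(x, y) = Σ|x−y| / Σ(x+y). Exchanging x and y changes nothing, so BC(T0, T1) = BC(T1, T0). Under within-participant permutation every permuted data set has the same set of participant distances as the observed one. Any statistic built on them is constant, and its permutation p-value is 1. This is algebra and rests on no simulation setting.

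**Step 4. Reading 2.** Dispersion at T0 and at T1 both exist, so a change can be defined. The arm-by-time term of a PERMANOVA compares locations, however, and is not designed to detect a change in spread.

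**Step 5. Can the targets disagree?** Simulation with 18 per arm, 60 taxa, log-normal abundances, 10,000 reads, 300 trials and 199 permutations. A t-test on BC(T0, T1), C versus D, was compared with the PERMANOVA arm-by-time pseudo-F. All abundance settings are assumed.

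| Scenario | Mean BC, C / D | Distance rejects | PERMANOVA, visits swapped within participant | PERMANOVA, whole participants permuted |
|---|---|---|---|---|
| Null | 0.230 / 0.229 | 0.053 | 0.050 | 0.053 |
| Same size, shared direction in C only | 0.229 / 0.230 | 0.100 | 1.000 | 1.000 |
| C moves further, random directions | 0.300 / 0.230 | 0.987 | 0.050 | 0.053 |

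Two further simulations under other assumed settings gave the same pattern with different sizes. A shared-direction shift was detected in 25% by the distance against 92% by the shift test, and in 22% against 67%. Idiosyncratic shifts were detected in 71% against 6.5%, and in 38% against 10%. The last figure suggests that the shift test can also react somewhat to unequal spread.

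**Step 6. Does the permutation scheme cause the disagreement?** No. The last two columns of the table nearly coincide, so the disagreement comes from what is measured. These scenarios contain no time change common to both arms, and so they do not show how the schemes compare when there is one. Swapping visits treats T0 and T1 as exchangeable, that is, no time change in either arm. Permuting arm labels needs only that the arms are exchangeable, which randomisation provides under the null.

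**The case against.** The best defence is that section 4.1 already settles the matter. It names Bray-Curtis, C against D, the T0-to-T1 change and PERMANOVA, and 3.2 says β-diversity was chosen to compare the groups' microbial composition. On that view reading 3 was always meant and 3.5.1 is only shorthand. This is plausible. If it is right, the test fits and 3.5.1 is what needs correcting. It does not remove the point, because the endpoint and its test are both fixed in this article and do not match as worded. That is more than detail left to an analysis plan.

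Several stronger readings are tempting and are not supported:

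- **Two rival confirmatory p-values.** Only PERMANOVA is prespecified. No section plans a test of individual T0-to-T1 distances.
- **The endpoint can have no T0 value.** That holds for the within-participant distance. Spread among participants does have a value at T0.
- **Section 4 prescribes a mixed model for the primary endpoint.** Its model text is general, for continuous outcomes, and does not name β-diversity.
- **The tests give opposite answers.** They can differ in that one rejects and the other does not. They do not give effects of opposite sign.
- **The simulated rates measure the risk in this trial.** The scenarios were built to separate the targets, and the rates vary widely with the settings.
- **The registry entry is wrong.** It is not among the documents.

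It is also fair that 3.2 calls a sample size calculation not strictly required for a pilot. The article nevertheless states 0.95 power in support of this endpoint, and that figure should attach to something defined.

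**Conclusion.** The point holds as a mismatch of definition between 3.5.1 and 4.1. Of three readings of the endpoint, PERMANOVA targets one. For the within-participant distance, the stated permutation scheme cannot provide a test at all, and this follows from symmetry alone. Across the three simulations, a shared-direction shift was detected in 10% to 25% of trials by the distance and 67% to 100% by the shift test. Idiosyncratic movement was detected in 38% to 98.7% and 5% to 10%. These ranges rest on assumed abundances and 18 evaluable participants per arm, and they show possibility, not probability. If f = 0.25 is attached to one number per participant, C versus D has power of about 0.31 to 0.34. If it is attached to a two-visit interaction with correlation 0.5, power is 0.83 to 0.87. The stated 0.95 is not established for the primary contrast in either case. The sponsor should settle the definition before any allocation-linked microbiome data are analysed.

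**What to change.** - **3.5.1:** restate the primary endpoint as the difference between C and D in the T0-to-T1 shift of Bray-Curtis community composition.
- **4.1:** name the arm-by-time PERMANOVA term as the primary test and report its R². Take the p-value from permuting arm labels between whole participants, within the randomisation strata (disease stage and age group, section 3.4.1), keeping each T0-T1 pair together. This matches the randomisation and is not affected by a time change common to both arms.
- **Secondary:** list the within-participant T0-to-T1 Bray-Curtis distance as a measure of magnitude of change, compared between arms by a participant-level test.
- **3.2:** say which quantity f = 0.25 refers to, or state that the 0.95 power does not apply to the PERMANOVA contrast of C versus D.
- **Registry:** align the entry only if it repeats the 3.5.1 wording.

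The cost is a few sentences in three sections and a short change to the analysis code. No new data, samples or visits are needed.
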